### Data Analysis

The analysis and reporting of results will be conducted in accordance with the **Consolidated Standards of Reporting Trials** guidelines adapted for cluster, randomized trials [37]. A blinded statistician will conduct analyses for primary and secondary outcomes. The primary analyses will be conducted with intention-to-treat principles. The primary outcome, FIC at 12 months of age, will be defined as a binary variable. Risk ratios for achieving FIC by 12 months of age will be calculated for the intervention arms as compared with the control arm. Due to the high number of clusters per study arm, individual level analyses using general estimating equations (GEE) with an exchangeable correlation matrix to account for correlation within clusters will be preferred over cluster level comparisons [38]. As a secondary analysis of the primary outcome, time-to-immunization curves will be constructed using the Kaplan-Meier method and study arms will be compared using the Cox model with frailty or robust variance estimator accounting for cluster. The 25th, 50th, and 75th percentiles for time to immunization and the number of days delayed, in relation to the EPI due date, will also be reported for each vaccine and by study arm. Lastly, adjusted analyses will be conducted if randomization results in imbalanced groups on key demographic variables. Effect estimates will be presented in whole and stratified on mobile phone ownership and clinic proximity. Mobile phone ownership will be defined as a binary variable (‘owns a mobile phone’ or ‘doesn’t own a mobile phone’). Socioeconomic quintile scores will be computed using a multiple correspondence analysis of household assets, livestock, water source, and cooking fuel [39]. Straight-line distances from the participant’s household to the nearest health facility will be calculated using ArcView Geographic Information Systems. An alpha of 0.05 will be assumed for all statistical tests of significance.

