### Setting and Participants

The M-SIMU study is located in Rarieda and Gem Districts of Siaya County, Kenya. Malaria, tuberculosis, and human immunodeficiency virus transmission are highly prevalent in this rural setting [33]. In 2008, the under-5 mortality rate was 212 deaths per 1000 live births, with pneumonia and diarrhea as common causes of childhood mortality [13].

The study site is nested within boundaries defined by KEMRI/CDC HDSS. Since 2001, the HDSS systematically collects information on births, deaths, migration, morbidity, and demographics every 4 months for a population of over 220,000 people. Within the HDSS, several disease specific studies have been conducted, including randomized controlled trials for bed-net efficacy, and rotavirus vaccine efficacy [34,35].

Prior to enrollment of the randomized controlled trial, a baseline survey was conducted in the study villages to obtain recent estimates of vaccination coverage for sample size calculation and to collect sociodemographic variables, such as mobile phone ownership and distance to nearest health facility, to perform a restricted randomization of study villages [16]. Additionally, three focus group discussions with 10 to 15 mothers who have a child 12- to 23-months-old were conducted to solicit local and contextual-specific feedback on the content and timing of the text message reminders, incentive amounts, willingness to receive reminders and incentives, and to anticipate any problems or complications associated with delivering text message reminders and incentives.

Villages are included in the cluster randomized controlled trial if they are located within either Gem or Asembo HDSS boundaries. Villages are excluded from the M-SIMU study if there are active immunization intervention/programs (e.g., nongovernmental organizations conducting immunization-related activities, outreach immunization clinics, etc.) that might confound study outcomes. Sample size calculations were conducted to determine the number of villages needed to be able to detect a 15% absolute difference in full immunization coverage at 12 months of age between control and intervention arms.

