### Secondary Objectives

The study assesses several secondary objectives that primarily focus on timely receipt of individual vaccines and effect modifiers on the primary outcome. These secondary objectives include:

1. To determine if FIC coverage measured at 10 months of age varies by study arm;

2. To determine if the proportion of children vaccinated within 2 weeks of each scheduled vaccine date differs by study arm;

3. To determine if the proportion of children who drop-out in vaccination between first and third pentavalent dose differs by study arm;

4. To determine if measles and or pentavalent3 vaccine coverage varies by study arm;

5. To determine if there is a differential effect on vaccine coverage based on mobile phone ownership (owned vs shared) or on residential distance from a health facility.

6. To determine whether other indicators of health status, such as height-for-age, bed-net usage, vitamin A coverage, retention of the maternal and child health card, and all-cause mortality vary by study arm; and

7. To evaluate the direct costs for each intervention arm per additional child vaccinated beyond the status quo (ie, control group).

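### Modification of the effect by distance is analysed only in clinic-proximity strata, although distance is measured continuously; an arm-by-distance interaction would usually have more power

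*Protocol article*

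**What the plan says.** Three statements in the protocol article bear on this point.

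- **The question.** Item 5 of Secondary Objectives asks whether the interventions work differently according to "mobile phone ownership (owned vs shared) or on residential distance from a health facility".
- **The measurement.** Data Analysis: "Straight-line distances from the participant’s household to the nearest health facility will be calculated using ArcView Geographic Information Systems". This gives one continuous value per household.
- **The analysis.** Data Analysis: "Effect estimates will be presented in whole and stratified on mobile phone ownership and clinic proximity".

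The same section adds, for the other modifier, "Mobile phone ownership will be defined as a binary variable", and gives its two categories. For proximity it states neither the number of strata nor where they are cut, and it names no arm-by-distance term. The primary model is a GEE with an exchangeable correlation matrix, clustered by village, and results are reported as risk ratios. Setting and Participants lists distance to the nearest health facility among the baseline-survey variables. Under Randomization, mean distance to the nearest clinic is one of the balance constraints.

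**The concern.** The objective asks about a gradient, the data can show a gradient, and the named analysis compares groups. Within a stratum all households are treated alike, so differences in distance inside it contribute nothing to the estimate of modification. If the effect changes steadily with distance, that information is lost. Power for any modification question is already limited here, because the trial was sized for a 15-point main effect and has 38 villages per arm.

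Distance is also not an incidental covariate. Under Interventions, the incentive is intended to help offset the cost of transport to the clinic, so distance is the modifier closest to the presumed mechanism. The Discussion says that the evidence is meant for health ministries deciding on scale-up. A missed gradient would leave them less well informed about where reminders or payments make most difference. The primary comparison is not touched.

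**Working it through.** **1. The plan's own sample size, to confirm the design inputs.** From Sample Size: 70% against 85%, alpha 0.05 (taken as two-sided), power 0.80, k = 0.25, and a harmonic mean of 16 children per village reduced by 25%, so m = 16 × 0.75 = 12.

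c = 1 + (z₀.₉₇₅ + z₀.₈₀)² × [p₀(1−p₀)/m + p₁(1−p₁)/m + k²(p₀² + p₁²)] / (p₀ − p₁)²

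= 1 + 7.849 × [0.21/12 + 0.1275/12 + 0.0625 × (0.49 + 0.7225)] / 0.0225

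= 1 + 7.849 × 0.1039 / 0.0225 = 37.25, rounded up to 38.

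The stated 38 villages per arm is reproduced. It does not bear on the distance question, but it supports using m = 12 and 38 villages per arm below.

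**2. Information kept by grouping.** If modification is linear in distance, the share of information kept is the between-stratum variance of distance divided by its total variance. The article gives no distance distribution, so several were assumed:

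| Assumed distribution | Median split | Tertiles | Quartiles |
|---|---|---|---|
| Uniform | 75% | 89% | 94% |
| Normal | 64% | 79% | 86% |
| Right-skewed (gamma, log-normal) | 55%, 52% | 72%, 67% | 79%, 75% |
| Exponential | 48% | 65% | 74% |

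The tertile and quartile columns assume that each group is scored by its mean distance. Power follows from Φ(√share × 2.80 − 1.96), given 80% for the continuous term. For a normal distribution and a median split this is Φ(√0.636 × 2.80 − 1.96) = 61%. Over all the distributions in the table the range is 49–68% for a median split, 62–75% for tertiles and 67–77% for quartiles.

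**3. Simulation with the trial's clustering.** One intervention arm against control, 38 villages per arm, 12 children per village. Assumed: normally distributed distance with 80% of its variance between villages, a gain of 8 points at average distance, and modification of 6 or 8 points per SD of distance. The analysis was a cluster-robust linear-probability model. Sample Size gives k = 0.14 as the baseline-survey value and 0.25 as the conservative value.

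Power (6 / 8 points):

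| Coding of distance | Linear, k = 0.14 | Linear, k = 0.25 | Step at the median, k = 0.14 |
|---|---|---|---|
| Continuous | 40% / 60% | 26% / 42% | 27% / 44% |
| Median split | 29% / 45% | 18% / 29% | 38% / 57% |
| Tertiles, 2-df test | 28% / 42% | – | – |
| Quartiles, ordered trend | 36% / 53% | – | – |

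In the step column the effect shifts by 6 or 8 points either side of the mean gain, exactly at the median distance. A repeat run of the same design agreed to within about four points throughout. With no true modification, each coding rejected in about 5–7% of runs, so differing test size does not explain the gaps.

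**4. Reading the results.** Under linearity at k = 0.14, the median split loses 11 to 15 points of power (40 − 29; 60 − 45) and ordered quartiles lose 4 to 7 (40 − 36; 60 − 53). Unordered tertiles do no better than the median split, because the test spends two degrees of freedom. With a step exactly at the cut the ranking reverses: the median split gains 11 to 13 points over continuous distance (38 − 27; 57 − 44).

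**The case against.** **The strata may be adequate.** The sentence says how estimates will be presented. It does not rule out a continuous term, and household distances are consistent with one. The number of strata is not given: only phone ownership is called binary. With ordered quartiles the loss is small. A threshold is also plausible, since transport cost may begin only beyond walking distance, and in that case strata can do better. All of this stands. It limits the point to a recommended improvement whose benefit depends on the shape of the effect.

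**A continuous term has its own hazards.** A form must be assumed. In one simulation with skewed, untransformed distance, the false-positive rate was 7.5%. This supports a log scale or a spline fixed in advance. The power of a spline was not simulated.

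**A stronger reading is tempting.** With no cut-point stated, a reader might infer that the cut will be chosen after outcomes are known and that a spurious near/far difference is therefore likely. Taking the best of seven candidate cuts did give nominal p < 0.05 in 18–21% of null simulations. The document does not support that inference. A condensed article may leave a subgroup cut to the full protocol or analysis plan, which is not shown. No passage suggests a search over cuts. Distance data existed before villages were allocated, so an early cut was possible. The article also says "A blinded statistician will conduct analyses for primary and secondary outcomes", which limits steering by direction of effect, though it would not prevent someone picking the smallest p-value. That figure is therefore not part of this finding.

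**Conclusion.** The point holds in a limited form. The article has a continuous modifier and a stated objective about it, and names only a stratified presentation. If modification is roughly linear in distance, continuous coding has more power: about 40% / 60% against 29% / 45% for a median split at k = 0.14, and 26% / 42% against 18% / 29% at k = 0.25, for 6 / 8 points per SD. The loss is smaller with ordered quartiles (36% / 53%).

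These figures rest on an assumed normal distance distribution, an assumed linear shape and assumed effect sizes. They are on the risk-difference scale with a linear-probability model, whereas the plan reports risk ratios from a GEE, so they show the order of the loss rather than its exact value.

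A reader might also conclude that the strata discard most of the information in distance. That cannot be said without knowing how many strata there are. Only one part of one secondary objective is affected, and even the continuous analysis has modest power in these scenarios, so a null result on distance would be weak evidence under either coding.

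**What to change.** In Data Analysis, state that the main assessment of modification by distance is an arm-by-distance interaction in the planned village-clustered GEE. Household distance should enter as a continuous variable, on the log-kilometre scale or as a spline with knots fixed in advance. Report each intervention arm's effect against control, with its confidence interval, at a few fixed distances.

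Keep the proximity strata as a display. Cut them at quantiles chosen without reference to outcomes, for example quantiles from the baseline survey. That requires the survey to hold the same household straight-line measure, which the article does not say. Otherwise, use quantiles of enrolled households' distances taken without regard to arm or outcome. As the article reports that follow-up is complete, date the change and record whether outcomes by arm had been seen.

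The cost is one or two sentences and no new data, because the household distances are already part of the plan. The downside is that a functional form must be assumed and the display is slightly less simple than a table by stratum. Showing the strata beside the fitted curve gives some protection if the true effect is a threshold.

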### Sample Size

The primary objective is to increase the proportion of infants that are fully immunized at 12 months of age by 15% (eg, a difference between 70% in the control arm and 85% in an intervention arm). There are few interventions available to public health officials that can rapidly raise immunization coverage by this amount so we expect that this size of an effect will represent a meaningful public health impact and could motivate decision makers to adopt this intervention. Type 1 error (alpha) and our power to detect a 15% difference (1-beta) were set to 0.05 and 0.80, respectively.

Village-level immunization coverage estimates were collected during the baseline survey. The baseline survey indicated that approximately 70% (1243/1681) of children were fully immunized by 12 months of age. This estimate was used for assumptions on control arm immunization coverage. Village size (m) was calculated using the most recent HDSS birth cohort data for our study area and assuming 1-year enrollment. Because our sample size per village varies, we computed the harmonic mean for village size, calculated to be 16 children per village. [40].

An important parameter in cluster sample size calculations is *k*, the between cluster coefficient of variation. Although our baseline survey indicated a *k*of 0.14, for sample size calculations we used a conservative estimate of 0.25.

We expect that the percentage of children who will not be enrolled due to not meeting eligibility criteria or refusal will be approximately 10% and the number who will be lost to follow-up after enrollment before 12 months of age, due to death, outmigration, and other reasons, will be 15%. Therefore, we used a 25% reduction from the birth cohort size to determine the number of villages we will enroll in the study.

In order to ascertain a 15% difference between control and intervention arms, 152 villages will be included in the study (38 villages per arm).

### Ethical Considerations

The study protocol received ethical clearance from the Scientific Steering Committee (SSC), the KEMRI-Nairobi Ethical Review Committee (ERC; SSC#2409), Johns Hopkins University Bloomberg School of Public Health (deferred ethical clearance to KEMRI-ERC), and the Centers for Disease Control and Prevention (deferred ethical clearance to KEMRI-ERC). The trial is registered with ClinicalTrials.gov [NCT 01878435, June 10, 2013]. The study’s principal investigators are authors DF and KO from Johns Hopkins University and FO from KEMRI/CDC.

## Results

The baseline survey was conducted March to April 2013 where it was found that 95% (2243/2393) of mothers owned or had access to a mobile phone within the compound. Focus group discussions were conducted in June 2013 to contextualize and adapt the interventions to the community’s needs and to identify the incentive amounts. The randomized-controlled trial completed enrollment in October of 2014. Twelve month follow-up visits to ascertain enrolled participants’ immunization status using the MCH booklet were completed in February, 2016.

## Discussion

Supply side strategies to improve immunization, such as improving cold chain capacity, increasing procurement, and staff training, have been effective, but immunization gaps persist. Demand side interventions, such as text message reminders and incentives, that target cost of transport, vaccine fears and perception, and forgetfulness may play a more prominent role in reaching the “last mile” with timely immunizations.

Despite a lack of rigorous scientific evidence of effectiveness, mHealth and conditional cash transfer programs continue to spread throughout Africa [41-43]. This is the first randomized study to evaluate the impact of text message reminders and mobile money incentives on immunization coverage within sub-Sahara Africa. Evidence generated by this project will assist decision makers in the Kenyan Ministry of Health, as well as those in other African countries, before committing the investment, time, and effort that will be necessary to scale-up these programs. Moreover, this project has the opportunity to demonstrate the potential of mobile phone technologies in achieving the Millennium Development Goal of reducing childhood mortality in Africa. We anticipate results in 2016.

## Appendix

Multimedia Appendix 1 Peer review summary report from scientific steering committee.

## Abbreviations

CDC: Centers for Disease Control and Prevention
CI: community interviewer
ERC: ethical review committee
FIC: fully immunized child
GEE: general estimating equation
HDSS: health and demographic surveillance system
HFR: health facility recorder
KEPI: Kenyan Expanded Programme on Immunization
KES: Kenyan Shilling
M-SIMU: Mobile Solutions for Immunization
MCH: maternal and child health
SSC: scientific steering committee
